## Abstract

**Background:**

Improving treatment uptake among people with chronic hepatitis B (CHB) infection who live outside urban centres is crucial to achieving the World Health Organization (WHO) elimination targets. Furthermore, as the number of deaths due to hepatitis B in Africa is rising, there is a need for new models of decentralized care adapted to the local context. The main aim of this study is to compare three different models of decentralized care for CHB treatment in Ethiopia, both from a clinical perspective and an implementation perspective.

**Methods:**

This will be prospective cohort study comparing three models of decentralized care for the management of CHB in Ethiopia. The first model (“standard model”) utilizes the current WHO guidelines for CHB management. The second model (“simplified model”) offers treatment to all individuals with CHB except those with a completely normal baseline assessment, and the third model (“test-and-treat model”) provides treatment to all individuals with CHB.

The study will enroll 4,500 individuals with CHB over a one-year period across six study sites in Ethiopia. All patients will be followed up for 3 years, and the primary outcome is death or liver failure. The three models will be compared using a Cox proportional hazards regression model adjusting for potential confounders.

Additionally, we will design adequate implementation strategies to address barriers and facilitators to implementation. We will design, implement and evaluate a policy toolbox that will ensure local adoption and implementation, using a co-creation approach, bringing together policymakers, politicians, healthcare personnel and patients, to come up with adequate policy implementation strategies for their contexts.

**Discussion:**

From a public health perspective, identifying a simple, feasible and effective model of decentralized CHB care would be a key step to reduce liver-related mortality on the African continent. This study may have important policy implications and is expected to inform national and international hepatitis B elimination efforts in low- and middle income countries (LMICs).

**Trial registration:**

ClinicalTrials.gov, NCT06586983. Registered on September 4, 2024.

## Background

Although the number of people newly infected by chronic hepatitis B (CHB) has declined in recent years, the estimated number of deaths due to CHB is increasing [1]. Over 60% of new hepatitis B infections occur in the World Health Organization (WHO) African region, but only 4% of people living with CHB have been tested in the same region [1]. Furthermore, treatment with Tenofovir disoproxil fumarate (TDF) or other nucleos(t)ide analogues (NA) can effectively prevent liver fibrosis and liver disease [2, 3], but only 0.2% of the estimated population with CHB in the WHO African Region are reached with treatment [1].

As identified by the WHO, a key challenge for LMICs to improve testing and treatment, is decentralization of care [1]. In Ethiopia, hepatitis B treatment and care is only available in larger cities [4, 5], while the majority of the population are living in rural areas [6]. With a population exceeding 100 million, and a hepatitis B prevalence at 6.0% [7], decentralized models of care are needed to reduce liver-related mortality. However, international CHB guidelines may not apply in this setting since modern tools such as hepatitis B virus (HBV) deoxyribonucleic acid (DNA) testing, liver stiffness measurements (LSM) or liver biopsy [8, 9] are unavailable in rural areas of Ethiopia. Previous studies have demonstrated how the lack of these tools can act as barriers to care [10]. Although the WHO has published an updated guideline with a simplified treatment algorithm [11], models of care suited to rural populations in LMICs with limited laboratory services and lack of specialized healthcare personnel are yet to be assessed. If the WHO elimination goals for viral hepatitis are to be reached [12], new models of CHB care tailored to these populations are needed.

In this study, we aim to test and compare three models of care at the primary care level in rural Ethiopia, and to explore and identify the best ways to implement CHB care and treatment in this setting. By testing three different models of care, and assesing both clinical and programmatic outcomes, we aim to identify the model of care best suited to rural poulations in LMICs. Furthermore, we plan to evaluate the implementation process, to identify barriers and facilitators, and to understand how to best implement a complex intervention in a resource-limited setting [13–16].

## Methods

### Study design

This will be prospective cohort study comparing three models of decentralized care for the management of CHB in Ethiopia. The overreaching research question is “What is the best model of care for testing, treatment, and follow-up in a primary hospital/health center in rural Ethiopia”. The three models of care will be assessed both from a clinical, programmatic and implementation perspective.

Testing, screening and linkage to care is common for the three model, but the treatment protocol differs. The standard model utilizes the WHO 2024 treatment guideline for hepatitis B to identify individuals at *high risk* of disease progression («*treat only if.*.») [11]. As most primary hospitals in Ethiopia lack assess to HBV DNA testing, we will use the WHO treatment eligibility criteria for settings without an HBV DNA analysis option (Table 1). The simplified model will utilize clinical and laboratory criteria to identify patients at *low risk* of liver injury, who will be exempted from treatment («*treat all except …*»). Finally, the test-and-treat model will offer treatment to all individuals with CHB (“*treat all*”), mimicking the models of care that have been successfully assessed and implemented for HIV and hepatitis C [17]. This latter model avoids the complicated patient assessment and the demand for expensive laboratory tests.

**Table 1 Tab1:** The three models of care to be assessed in the study: treatment criteria, laboratory analyses required, and scheduled follow-up

	Standard model “treat only if…”	Simplified model “treat all except…”	Test and treat model “treat all”
Treatment criteria	Treat *only* if:	Treat all, *except* if:	Treat all
	-Clinically diagnosed cirrhosis	-There are no signs, symptoms or risk factors for liver disease, *AND*	
	-APRI above 0.5	-APRI is 0.3 or below	
	-Persistently elevated ALT		
	-Co-infections and co-morbidity		
	Pregnant women: treat to prevent mother-to-child transmission		
Laboratory analysis required at inclusion	AST, ALT, platelets, (Creatinine^1^)	AST, platelets (Creatinine^1^)	(Creatinine^1^)
	HIV, HCV, HBsAg RDTs	HIV, HCV, HBsAg RDTs	HIV, HCV, HBsAg RDTs
Follow-up:on treatment	Physical examination, HIV, and pharmacy refill at 3 months, then every 6 months	Physical examination, HIV, and pharmacy refill at 3 months, then every 6 months	Physical examination, HIV and pharmacy refill at 3 months, then every 6 months
	AST, ALT, platelets, (creatinine^1^), HBsAg, DBS every 12 months	AST, platelets, (creatinine^1^), HBsAg, DBS every 12 months	(Creatinine^1^), HBsAg, DBS every 12 months
Follow-up:*not* on treatment	Physical examinationAST, ALT, plateletsHBsAg,DBSevery 6 months	Physical examinationAST, plateletsHBsAg,DBSevery 6 months	N/A

*Abbreviations**: ALT* alanine aminotransferase, *APRI* aspartate aminotransferase to platelets ration, *AST* aspartate aminotransferase, *HCV* hepatitis C virus, *HbsAg* hepatitis B surface antigen, *HIV* human immunodeficiency virus, *DBS* dried blood spot testing, *N/A* Not applicable, *RDT* rapid diagnostic test

^1^ Only required in patients at risk of renal disease, i.e. individuals with hypertension, diabetes, use of nephrotoxic drugs, or age above 60 years

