### Objectives

*Study clinical efficacy (death*,* liver decompensation) of different models of decentralized CHB care*.*Study programmatic success indicators (linkage to care*,* loss to follow-up) with different models of decentralized CHB care*.*Evaluate the implementation of CHB care (Context*,* process*,* and outcomes) of different models*.*Study laboratory success indicators (suppression of viral load*,* human immunodeficiency virus (HIV) incidence) in different models of decentralized CHB care*.*Compare all outcome indicators (points 1–3 above) of decentralized care with the results of hospital-based care from similar settings*.*Study the effect of community screening for hepatitis B*.

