### Screening activities

Screening for HBsAg at the various sites will be conducted as determined by the local teams, and will include screening at the hospital premises, at local schools, markets, factories, or religious institutions. Rapid diagnostic tests (RDTs) will be used for screening, based on availablility. A confirmatory test will be done at enrolment in the CHB programme. After initial screening, HBsAg positive individuals will counselled and referred to the HBV clinic for HBsAg confirmation testing using the WHO prequalified Determine HBsAg 2 RDT (Abbott Diagnostics, IL, USA) and enrolment in CHB care. All HIV negative adults>18 years with a positive HBsAg confirmation test are eligible for inclusion. Those who are found to be HIV positive at baseline will be referred to the local HIV treatment unit, and not be enrolled in the present project.

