### Outcomes 

The primary endpoint will be either death or liver decompensation (composite endpoint). Liver decompensation will be detected clinically (ascites, jaundice, encephalopathy, upper gastrointestinal bleeding). Deaths will be verified by health extension workers, who will trace/identify patients WHO miss appointments for more than 3 months. Health extension workers are individuals with a minimum of 10^th^ grade schooling who are part of the Ethiopian public health extension program. Each village has two health extension workers whose main responsibility is to deliver preventative and promotive health services at community level.

Secondary endpoints include programmatic outcomes (linkage to care, retention in care) and laboratory outcomes (viral suppression *viz*HBV DNA ≤10 IU/ml; new HIV infection). HBV DNA is not part of routine care at these sites but will be collected using dried blood spots (DBS) during the study period and measured after completion of the observation period (three years) for those who have received treatment, using the Xpert HBV viral load kit (Cepheid, CA, USA). 

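### HIV incidence is to be studied across the three models, but Table 1 schedules follow-up HIV tests only for patients on treatment, so case-finding follows treatment status

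*Protocol article*

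**What the plan says.** **Objective and endpoint.** The fourth item under Objectives covers laboratory indicators, including "human immunodeficiency virus (HIV) incidence) in different models of decentralized CHB care". The Outcomes section lists "new HIV infection" among the secondary laboratory endpoints. The same section limits HBV DNA measurement to participants who received treatment, but attaches no such limit to HIV.

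**Population at risk.** Under Screening activities, "All HIV negative adults>18 years with a positive HBsAg confirmation test are eligible for inclusion". Table 1 (Study design) requires "HIV, HCV, HBsAg RDTs" at inclusion in every model. Everyone enrolled is therefore HIV negative at entry and can contribute to incidence.

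**Follow-up, on treatment (Table 1).** The standard and simplified columns read "Physical examination, HIV, and pharmacy refill at 3 months, then every 6 months"; the test-and-treat column has the same content.

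**Follow-up, not on treatment (Table 1).** Standard model: "Physical examinationAST, ALT, plateletsHBsAg,DBSevery 6 months". Simplified model: "Physical examinationAST, plateletsHBsAg,DBSevery 6 months". Neither cell contains HIV. The test-and-treat cell is marked not applicable, because "the test-and-treat model will offer treatment to all individuals with CHB".

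No other section schedules HIV testing for untreated participants. The only stated use of the dried blood spots (DBS) is HBV DNA, measured at the end of the observation period in those who received treatment.

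**The concern.** The three models differ in who is treated, and Table 1 makes scheduled HIV testing depend on being treated. The chance of finding a new infection therefore differs between models by design, even if true incidence is the same.

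An analyst has two obvious denominators, and each has a problem. Counting over everyone enrolled misses infections in untreated patients of the standard and simplified models, which makes test-and-treat look worse on HIV. Counting only over treated patients closes the detection gap, but sets patients selected by liver-related and other criteria in two models against an essentially unselected group in the third. What is at stake is a secondary outcome that could produce a misleading signal against one model of care.

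**Working it through.** The documents give no figure for the HIV endpoint: no expected incidence, no treated share and no planned contrast. There is nothing to reproduce. The check is a reading of the schedule, followed by an illustration on stated assumptions.

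**1. Scheduled follow-up HIV tests by model and treatment status (Table 1)**

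- Standard: on treatment, yes; not on treatment, none.
- Simplified: on treatment, yes; not on treatment, none.
- Test-and-treat: on treatment, yes; not on treatment, no schedule (not applicable).

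**2. Denominator: everyone enrolled**

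Let *f* be the share of a model's person-time that is on treatment and hence on the tested schedule. Suppose true incidence is equal in all patients, treated or not, and infections are found only by scheduled tests. Recorded incidence is then about *f* × true incidence, so

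recorded ratio (test-and-treat : other model) = *f*(test-and-treat) / *f*(other model).

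All values of *f* are assumptions.

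- Standard, *f* = 0.5 to 0.3, full uptake in test-and-treat: 1/0.5 = 2.0 to 1/0.3 = 3.3.
- Simplified, *f* = 0.8 to 0.5, full uptake in test-and-treat: 1/0.8 = 1.25 to 1/0.5 = 2.0.
- Standard, *f* = 0.5 to 0.3, with 80% uptake in test-and-treat: 0.8/0.5 = 1.6 to 0.8/0.3 = 2.7.

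**3. The same in counts**

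Inputs: 1,500 participants per model and 3 years (Sample size and duration of the study); assumed incidence of 0.3 per 100 person-years in every model; no attrition.

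- True infections per model: 1,500 × (1 − exp(−0.003 × 3)) = 13.4.
- Found with treated shares of 30% / 60% / 100% (standard / simplified / test-and-treat): 13.4 × 0.3 = 4.0; 13.4 × 0.6 = 8.1; 13.4.

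About 4 against 13 recorded infections would then arise with no true difference.

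**4. Why these ratios are upper-end values**

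A patient who starts treatment later is tested from then on, and those tests also reveal infections acquired earlier, so the share found exceeds the share of person-time on treatment. Incomplete uptake in test-and-treat lowers the numerator, as the 80% line shows. Detection outside the schedule raises the count in the under-tested models. Each of these brings the ratio closer to 1.

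**5. Denominator: treated patients only**

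The detection gap disappears. In the standard model, however, treated patients are those with cirrhosis, raised APRI, lasting ALT elevation, co-infection or co-morbidity, or pregnancy. In the simplified model they are all but those without signs, symptoms or risk factors and with a low APRI. In test-and-treat there is no selection criterion. The documents do not allow the direction or size of the resulting confounding to be determined.

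**6. With the gap closed**

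If untreated participants are also tested at their visits, *f* is close to 1 in every model and the expected ratio under equal incidence is about 1.0.

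**The case against.** **No explicit contrast is planned.** Objective 4 says to study HIV incidence, not to compare it. The objective that does speak of comparing covers points 1-3 only. The Statistical analysis section specifies a between-model analysis only for death or decompensation, and a data analysis plan is still to come. This stands in part: no biased analysis has been fixed. But the objective refers to different models, the study exists to compare them, and the data to be collected cannot support a fair comparison whichever analysis is later chosen.

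**On-treatment incidence may be what is meant.** Table 1 puts HIV beside the pharmacy refill, and the companion endpoint, HBV DNA, is restricted to treated patients. This is plausible, but the restriction is written for HBV DNA and not for HIV. If it is intended, it needs to be stated.

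**The article is condensed.** A shortened table row could explain the gap. However, Table 1 itemises each cell and names HIV in one row but not the other. That is a stated schedule that does not fit a stated endpoint, rather than a detail left out.

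**Stronger readings to avoid.** A reader might infer that any HIV difference would be purely an artefact. The documents support only that it would be biased, since a true difference could contribute. A reader might also infer that a fixed number of standard-model patients is never retested. Blood tests are repeated every six months, and pregnant women receive antivirals in all models (Pregnant women section), so some initially untreated patients will move onto the tested schedule. Finally, treated patients in the standard model might be taken to be at high risk of HIV. Most of the criteria concern liver disease, and the documents tie none of them to HIV acquisition.

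**Conclusion.** The point holds as a mismatch between endpoint and schedule. As written, scheduled ascertainment of new HIV infection depends on treatment status, and treatment status is what distinguishes the models. Over all enrolled, the standard and simplified models are under-counted relative to test-and-treat. Over treated patients only, differently selected groups are compared.

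The direction of the first bias follows from the schedule; its size does not. The range of about 2.0-3.3 for test-and-treat against standard is an upper-end illustration. It rests on 30-50% of standard-model person-time being on treatment, equal true incidence, fixed treatment status, full uptake in test-and-treat and no detection outside the schedule. It should not be read as an estimate.

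The primary endpoint, the sample size and the main Cox analysis are unaffected. The mismatch should be corrected, but it does not threaten the study's main result.

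**What to change.** Reconcile Table 1 with the Objectives and Outcomes sections in one of two ways.

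1. **Measure it in everyone.** Add the HIV rapid test already used at inclusion to the existing six-monthly visits of untreated participants in the standard and simplified models. The cost is the tests and a little staff time; no new visits are needed. If the on-treatment schedule is read as months 3, 9, 15 and so on, the test dates will not coincide with months 6, 12, 18. Counting person-time only up to each participant's last HIV test deals with most of this. Enrolment began in September 2024, so early action matters, although a later first retest still reveals earlier infections in those who attend, with less exact timing.

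2. **Narrow the claim.** Define the endpoint as descriptive on-treatment HIV incidence per tested person-year and make no between-model claim. This costs nothing, but gives up HIV incidence as a comparison across models.

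Testing stored DBS for HIV is an option only if the samples and the consent allow it, which the documents do not state. An assay at study end could also identify infections up to three years late.

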### Objectives

*Study clinical efficacy (death*,* liver decompensation) of different models of decentralized CHB care*.*Study programmatic success indicators (linkage to care*,* loss to follow-up) with different models of decentralized CHB care*.*Evaluate the implementation of CHB care (Context*,* process*,* and outcomes) of different models*.*Study laboratory success indicators (suppression of viral load*,* human immunodeficiency virus (HIV) incidence) in different models of decentralized CHB care*.*Compare all outcome indicators (points 1–3 above) of decentralized care with the results of hospital-based care from similar settings*.*Study the effect of community screening for hepatitis B*.

### Study setting

The study will be established at six primary hospitals and health centers in rural Ethiopia (Fig. 1), and will leverage on research infrastructure at Addis Ababa University and St Paul’s Hospital Millennium Medical College in Addis Ababa. Three study sites were selected from the Oromia region due to its relative ease of access from Addis Ababa for training of staff, shipment of drugs and equipment, and travel for the study teams. Another three study sites were selected from the Somali region in Ethiopia, which were chosen based on previous collaboration with the local health authorities and the relatively stable geopolitical situation. In total, the Oromia and Somali regional states have > 100 primary hospitals and > 1500 health centers serving a predominantly rural population of approximately 44 million people [18, 19]. Primary hospitals and health centers usually offer outpatient and inpatient services, maternal and child facilities including antenatal care (ANC), emergency surgery, HIV clinics, and access to basic laboratory services such as alanine aminotransferase (ALT), aspartate aminotransferase (AST), hematology (including platelets). A primary hospital typically serve between 60,000 and 100,000 inhabitants.

**Fig. 1 Fig1:**
[figure not shown]
Map of Ethiopia, with the 12 regional states. The study sites are illustrated with red dots. Original image from www.wikipedia.com, reproduced and adapted accordinly to the creative commons attribution-share alike 4.0 international license (https://commons.wikimedia.org/wiki/File: Regions_of_Ethiopia_EN.svg)

Two sites will be assigned to the standard model of care («treat only if…»), two sites to the simplified model of care («treat all except…»), and two sites to the test-and-treat model («treat all»). Each model will include one site situated in the Oromia region and one in the Somali region.

The final selection of the study sites were done in close collaboration with the regional health bureaus in the Oromia and Somali regions. As the study aimed to assess care in rural areas, primary hospitals or health centers in rural areas of these regions were considered. Only primary hospitals or health centers having an ART clinic were considered, leveraging the capacity for screening, counselling, initiation of antiviral treatment, long-term follow-up, and tracing efforts in cases of loss to follow-up. Furthermore, sites assigned to the standard or simplified model were required to have access to standard laboratory services such as hematology and biochemistry (ALT, AST) analysis.

Thus, participants will be recruited from the following six sites:

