#### Standard model of care

Mojo district hospital (Oromia region) has approximately 80 beds and has an established HIV clinic caring for approximately 250 individuals. The hospital is located 179 km from Addis Ababa, and has a catchment population of approximately 70,000 individuals ([name]: Regional database. Oromia Regional Health Bureau, Addis Ababa, Ethiopia, personal communication). The hospital has access to basic laboratory services including biochemistry.

Degehabur hospital (Somali region) is situated in Degehabur town with approximately 48,000 inhabitants [19]. It provides internal medicine, general surgery, paediatrics, gynecology/obstetrics, and has an HIV clinic. This primary hospital has a catchment area of approximately 1,000,000 inhabitants from a vast and scarcely populated area ([name]: Regional database. Somali Regional Health Bureau Jigjiga, Ethiopia, personal communication).

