#### Simplified model of care

Batu general hospital (Oromia region) is located in Batu town, in the East Shewa zone, approximately 160 km from Addis Ababa. The town has approximately 80 000 people [19]. The hospital has 60 beds, and has a well-functioning HIV clinic.

Gode general hospital (Somali region) is located in the Shabelle zone, and has a catchment area of approximately 1,500,000 inhabitants ([name]: Regional database. Somali Regional Health Bureau Jigjiga, Ethiopia, personal communication). The main in-patient services at the hospital are medical, surgical, pediatrics, orthopedics, gynecology-obstetrics, dermatology, psychiatry, intensive care, and a malnutrition center. The hospital also runs an HIV clinic.

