#### Test-and-treat model of care

Sebata health centre (Oromia region) lies in the south west Shewa zone around 40 km from Addis Ababa. The center employs 40 clinical staff (including one physician), and has an HIV clinic providing care to 1200 patients. The catchment area of the health center is approximately 50,000 individuals ([name]: Regional database. Oromia Regional Health Bureau, Addis Ababa, Ethiopia, personal communication).

Biki general hospital is located in Biki town with approximately 10,000 inhabitants [19]. The town lies 250 km from Jigjiga, the capital of the Somali region, but with limited access due to poor road conditions. The hospital has a catchment population of approximately 300,000 ([name]: Regional database. Somali Regional Health Bureau Jigjiga, Ethiopia, personal communication), and has basic laboratory services such as biochemistry and a well-run HIV clinic.

Each study site will have a team composed of 3-5 individuals responsible for screening, inclusion, delivery of the intervention, and follow-up of participants. This will typically be one medical doctor (or health officer), one nurse, one laboratory technician and one data clerk. Team composition will depend on location, accesibility of personnel, and experience of those identified. The study teams will be identified by the local study site and fully integrated into existing clinical infrastructure at the sites. The study aims to utilize existing staff employed at the local health centers/hospitals.

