### Sample size and duration of the study

The sample size has been calculated for the primary outcome (death or liver decompensation) with 80% power and 5% risk of type I error. We anticipate that 5% of all included patients (treated and untreated) will either die or experience liver decompensation within 3 years, with the standard model [20], and we want to detect a 50% relative reduction (Odds Ratio of 0.5 or less) with the test-and-treat model. This results in a sample size of 997 patients per arm [21]. We will increase the sample size by 50% and aim for 1,500 patients per model of care arm, due to expected attrition. This results in a total of 4,500 patients at six different sites. Assuming that approximately 9% of those living in the study setting are hepatitis B surface antigen (HBsAg) positive and 50% of those screened can be included in the study, we estimate that we need to screen approximately 100,000 individuals in order to enroll 4,500 CHB patients.

As inclusion rates may vary across sites, we plan to continue inclusion until all models of care have reached 1500 inclusions, accepting an uneven distribution between the two clinics assigned to the model. We expect to complete inclusion within 1 year. As the observation period will be three years, the total study period will be four years. The first participant was enrolled at September 5, 2024, and recruitment is ongoing. 

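### The one health centre is the Oromia test-and-treat site, and the planned Cox model has no region term, so the pooled hazard ratio can mix model of care with facility type and regional mix

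*Protocol article*

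**What the plan says.** The Study setting section gives each model one Oromia site and one Somali site. It limits selection by clinic type ("Only primary hospitals or health centers having an ART clinic were considered") and adds that "sites assigned to the standard or simplified model were required to have access to standard laboratory services". No laboratory requirement is stated for test-and-treat sites.

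The site descriptions give:

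| Model | Oromia | Somali |
|---|---|---|
| Standard | hospital: "Mojo district hospital (Oromia region) has approximately 80 beds" | hospital (Degehabur) |
| Simplified | hospital, 60 beds: "Batu general hospital (Oromia region) is located in Batu town" | hospital (Gode) |
| Test-and-treat | health centre: "Sebata health centre (Oromia region) lies in the south west Shewa zone around 40 km from Addis Ababa" | hospital (Biki) |

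Of the health centre the article says: "The center employs 40 clinical staff (including one physician"). Of the Somali test-and-treat hospital it says that it "has basic laboratory services such as biochemistry and a well-run HIV clinic".

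Under Sample size and duration, inclusion continues until each model reaches 1,500, "accepting an uneven distribution between the two clinics assigned to the model".

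Under Statistical analysis, the primary analysis is a Cox model for model of care, adjusted for baseline covariates that include age, sex and liver cirrhosis. It is accompanied by unadjusted Kaplan-Meier curves, a log-rank test and one worst-case sensitivity analysis for missing outcomes. Region, site and facility type are not named.

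**The concern.** Two features of the design can enter the test-and-treat versus standard hazard ratio, which is the contrast that sets the sample size.

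First, facility type. No standard or simplified participant is seen at a health centre. In Oromia the comparison of models is therefore also a comparison of a health centre with hospitals. No covariate can separate the two, because a facility-type term would rest on a single site.

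Second, regional mix. The design matches the models on region, but enrolment is fixed only per model. If the models end with different Oromia:Somali proportions and the regions differ in baseline risk, an analysis that pools over region carries that difference into the model effect. The matching is built into the design but not used in the stated analysis.

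The results are meant to inform national and international policy. A hazard ratio that depends on one health-centre comparison, or on how enrolment happened to fall between regions, could be read as an effect of the treatment rule.

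**Working it through.** **The plan's own figure.** Inputs from Sample size and duration: 5% three-year risk under the standard model, a 50% relative reduction, 80% power, 5% type I error. Two-sided comparison of 5% with 2.5%:

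- n = [1.96·√(2·0.0375·0.9625) + 0.842·√(0.05·0.95 + 0.025·0.975)]² / 0.025² = 906 per arm
- with continuity correction: 984 per arm

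The second is within 1.3% of the stated 997, and 997 × 1.5 = 1,495.5, rounded to 1,500. The figure is not in dispute; 997 is used below as the number per model after the planned attrition allowance.

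**Facility count.** Standard: 2 hospitals, 0 health centres. Simplified: 2 and 0. Test-and-treat: 1 and 1. The only contrast in which every site is called a hospital and the regions match is the Somali one.

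**Regional mix (assumed risks: Oromia 4%, Somali 6%, no effect of model).** Pooled risk = share in Oromia × 4% + share in Somali × 6%.

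- Standard, 50:50: 0.5 × 4% + 0.5 × 6% = 5.0%
- Test-and-treat, 80:20 towards Oromia: 0.8 × 4% + 0.2 × 6% = 4.4%; risk ratio 4.4/5.0 = 0.88
- Test-and-treat, 20:80: 0.2 × 4% + 0.8 × 6% = 5.6%; risk ratio 1.12

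Equal splits in the two models give 1.00. Within each region the ratio is 1.00 whatever the split, which is why stratifying by region removes this component.

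**Facility type (assumed; hospital risk 5%, no effect of model).** Test-and-treat risk = share at health centre × health-centre risk + remainder × 5%. The health-centre risk is not in the documents, so it is varied both ways:

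| Health-centre risk | 50:50 split | 80:20 towards health centre |
|---|---|---|
| 3% | 4.0%, RR 0.80 | 3.4%, RR 0.68 |
| 4% | 4.5%, RR 0.90 | 4.2%, RR 0.84 |
| 6% | 5.5%, RR 1.10 | 5.8%, RR 1.16 |
| 7% | 6.0%, RR 1.20 | 6.6%, RR 1.32 |

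At 997 per model, the chance of a nominally significant result with no true effect is about 19% and 42% in the 3% row and about 8% and 14% in the 4% row, against a nominal 5%. (Log odds ratio with variance 1/(n₁p₁q₁) + 1/(n₂p₂q₂).)

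**Precision of the Somali contrast.** Odds ratio 0.5 from 5% gives 2.564%. Power = Φ(0.693/SE − 1.96), with SE from the same variance formula:

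| Standard | Test-and-treat | SE | Power |
|---|---|---|---|
| 500 | 500 | 0.350 | 51% |
| 750 | 750 | 0.285 | 68% |
| 500 | 200 | 0.492 | 29% |
| 750 | 300 | 0.402 | 41% |

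The first two rows are a half share of about 1,000 (after attrition) or 1,500 (without). The last two put 20% of test-and-treat at the Somali site. Clustering is ignored throughout, so these are optimistic.

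**The case against.** Several stronger readings are tempting, and the documents do not support them.

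*That the assignment rule ties facility level to model.* The rule concerns laboratory access. The Study setting section says that primary hospitals and health centres alike usually have ALT, AST and platelets, so the rule does not bar a health centre from any model. The health centre's own laboratory is not described, and the Somali test-and-treat hospital has biochemistry. What the documents show is one site of a different type.

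*That the bias favours test-and-treat.* One might infer that hospitals draw sicker patients and detect more decompensation. But screening also takes place at schools, markets, factories and religious institutions; each site has a similar team of 3-5; decompensation rests on the same four clinical signs everywhere; and deaths are verified by health extension workers. Fewer clinicians could equally mean worse outcomes, while an HIV clinic with 1,200 patients, against about 250 at the standard Oromia hospital, could mean more experience of chronic care. The sign is open.

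*That an effect seen only in Oromia should not be credited to the model.* With 29-68% power in the Somali region, such a rule would often discard a real effect.

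It can also be said that the covariate list is open, that a data analysis plan is still to be written, and that the Discussion concedes that baseline comparability across models is not ensured. This stands to a degree: the mere absence of a sensitivity analysis from an article is not the point. However, the concession does not mention facility type, and what the article does fix (sites matched by region, an open split, a pooled model effect) leaves the matching unused.

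Finally, the Somali contrast sets one site against one site, with catchments of about 300,000 and 1,000,000 and possibly different hospital levels. That objection stands and limits what the contrast can show.

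**Conclusion.** The point holds in a limited form. In Oromia, facility type cannot be separated from the test-and-treat model; the direction and size of any resulting bias are unknown, and the facility-type figures above are illustrations on assumed risks. Separately, the pooled analysis is exposed to differences in regional mix: risk ratio 0.88 or 1.12 with no true effect, if regional risks are 4% and 6% and one model is split 80:20 or 20:80 against 50:50 in the other. The second problem can be removed in the analysis. The first cannot, but region-specific estimates would show whether the pooled result depends on the one health-centre comparison. This is worth acting on before the analysis plan is written, but it does not invalidate the study.

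**What to change.** 1. Stratify the primary Cox model and the log-rank test by region.
2. Report the test-and-treat versus standard hazard ratio for Oromia and for Somali, each with a 95% CI, and present the Somali (hospital-only) contrast as a sensitivity analysis.
3. State as a limitation that in Oromia facility type is confounded with model of care.
4. Say in advance that discordant regional estimates call for cautious interpretation, without a rule that accepts or discards an effect.

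The cost is wording and two extra estimates; no new data are needed, and the article describes recruitment as ongoing with the analysis plan still to come. The limits should be stated alongside. The Somali contrast has about 51-68% power for an odds ratio of 0.5 at 500-750 per model, and about 29-41% if only 200-300 test-and-treat patients are enrolled there, before clustering. It rests on one site per model, so site effects remain. Stratifying by region does not by itself remove the facility difference in Oromia.
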